### Outcome measures

#### Questionnaires

The outcome measures will be assessed by standardized questionnaires with good psychometric qualities and available normative data (Table 2) [26, 54–63]. To assess participants’ satisfaction with the intervention, content, design and course leaders, participants in the intervention group complete an evaluation questionnaire at the end of the intervention period (T1).

**Table 2 Tab2:** Primary/secondary outcome measures, measurements and informant for the adolescent and parent intervention

	Measurements	Informant
Primary outcome measures		
Adolescents		
Psychosocial functioning	Child Behavior Checklist (CBCL) and Youth Self Report (YSR)	Parent and adolescent
Disease-related coping skills	*Op Koers* Questionnaire (OKQ)	Adolescent
Parents		
Psychosocial functioning	Hospital Anxiety and Depression Scale (HADS)	Parent
Disease-related coping skills	*Op Koers* Questionnaire (OKQ)	Parent
Secondary outcome measures		
Adolescents		
Self-esteem	Perceived Competence Scale for Adolescents (CBSA)	Adolescent
Quality of Life	Pediatric Quality of Like Inventory - self report (PedsQL)	Adolescent
Parents		
Impact of the illness on family functioning	Pediatric Quality of Life Inventory - Family Impact Module (PedsQL-FIM)	Parent
Parental distress	Distress Thermometer for Parents (DTP)	Parent
Social involvement	Inventory Social Involvement (ISI)	Parent
Illness cognitions	Illness Cognition Questionnaire for Parents (ISQ)	Parent

### Statistical analyses

Analyses will be performed according to the intention-to-treat principle. Primary and secondary outcomes will be assessed with linear mixed model analyses using SPSS. The intervention is qualified as effective if the intervention group improved more over time on one of the primary outcomes than the control group, at a significance level of 0.05 and at small to medium effect size d [0.2–0.5].

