**Methods/design:**

This study conducts two separate multicenter randomized controlled trials. Participants are adolescents (12 to 18 years of age) with CI and parents of children (0 to 18 years of age) with CI. Participants are randomly allocated to the intervention group or the waitlist control group. Outcomes are measured with standardized questionnaires at baseline, after 8 (adolescents) or 6 (parents) weeks of treatment, and at 6- and 12-month follow-up period. Primary outcomes are psychosocial functioning (emotional and behavioral problems) and disease-related coping skills. Secondary outcomes for adolescents are self-esteem and quality of life. Secondary outcomes for parents are impact of the illness on family functioning, parental distress, social involvement and illness cognitions. The analyses will be performed according to the intention-to-treat principle. Primary and secondary outcomes will be assessed with linear mixed model analyses using SPSS.

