**Discussion:**

These randomized controlled trials evaluate the effectiveness of two online group interventions improving psychosocial functioning in adolescents with CI and parents of children with CI. If proven effective, the intervention will be optimized and implemented in clinical practice.

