First, the intervention for survivors of childhood cancer was developed. A pilot study on the feasibility of *Op Koers Online Oncology* for adolescent survivors showed promising results [39]*.* The intervention was optimized based on feedback from participants and course leaders (for example: expanding the sessions from six to eight). After that, *Op Koers Online* for adolescents with CI was developed. Similar to the face-to-face intervention, goal is to prevent and/or reduce psychosocial problems by teaching the use of active coping skills with CBT techniques. Sharing experiences with other chronically ill adolescents is an important part of the intervention. First pilot results on the feasibility and potential effectiveness of *Op Koers Online* for adolescents with CI are promising ([name] et al.: Feasibility and effectiveness of an online cognitive-behavioral based group intervention for adolescents with chronic illness, submitted).

For parents, most existing interventions focus on the child’s functioning [13, 22]. The same applies to *Op Koers* face-to-face for parents, where participating parents learn what their child learns and how to support their child in implementing coping skills in daily life [32, 34]. However, research suggests the need of emotional, informational and peer support for parents [41, 42]. For the development of *Op Koers Online* for parents, the Emma Children’s Hospital (Academic Medical Center, Amsterdam) conducted a survey among parents on their specific wishes and needs. The need for an intervention focusing on parental functioning instead of focusing only on the child emerged from the survey. Based on the results of this survey, *Op Koers Online* for parents of children with CI was designed.

This paper describes the rationale and the design of two separate multi-center randomized controlled trails aimed to assess the extent to which *Op Koers Online* is effective in preventing and/or reducing psychosocial problems (emotional/behavioral problems and quality of life) and improving the use of disease-related coping skills in adolescents with CI (12–18 years) and in parents of children and adolescents (0–18 years) with CI.

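### The rule for declaring the intervention effective is met by one improved primary outcome even if psychosocial functioning is significantly worse, and it does not match the Discussion's condition for implementation

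*Protocol article*

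**What the plan says.** The abstract's Methods/design paragraph names two primary domains: "Primary outcomes are psychosocial functioning (emotional and behavioral problems) and disease-related coping skills". Table 2 assigns the instruments. Adolescents have the CBCL (parent report) and YSR (self-report) for psychosocial functioning and the *Op Koers* Questionnaire (OKQ) for coping, so three measures. Parents have the HADS and the OKQ, so two.

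The Statistical analyses section then gives a decision rule: "The intervention is qualified as effective if the intervention group improved more over time on one of the primary outcomes than the control group". The same sentence adds two conditions, namely significance at the 0.05 level and an effect size d between 0.2 and 0.5. Nothing is asked of the other primary outcome or outcomes.

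Three other statements bear on the rule:

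- The Background says of the adolescent course that the "goal is to prevent and/or reduce psychosocial problems by teaching the use of active coping skills with CBT techniques". The section on the parent course gives the same aim. Coping is the means and fewer psychosocial problems the end.
- The Background's objective for both trials is to learn how far the course "is effective in preventing and/or reducing psychosocial problems (emotional/behavioral problems and quality of life) and improving the use of disease-related coping skills".
- Implementation is described twice. The abstract's Discussion says: "If proven effective, the intervention will be optimized and implemented in clinical practice". The closing paragraph of the main Discussion makes it depend on significant effects on psychosocial wellbeing and on disease-related coping skills.

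**The concern.** The OKQ is the primary measure closest to what is taught, since the learning goals of both courses are greater use of named coping skills. Under the rule as written, a significant OKQ gain settles the matter. A simultaneous significant worsening on the HADS, YSR or CBCL would leave the label *effective* untouched, and in the abstract that label is what leads to implementation.

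This differs from the number of tests. Adjusting alpha across the primaries limits false claims of benefit, but it would still pass a trial with one adjusted gain and one significant deterioration.

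At stake is what happens if the outcomes diverge. The rule would say effective, the Discussion's joint condition would say not ready to implement, and someone would have to choose between them after seeing the data.

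**Working it through.** **1. The statements side by side**

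| Place | What is required |
|---|---|
| Statistical analyses | improvement on one primary, p < 0.05, d 0.2–0.5 |
| Abstract, Discussion | proven effective, then implemented |
| Main Discussion, last paragraph | significant effects on wellbeing and on coping, then implemented |

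Suppose the OKQ is significantly better and the HADS significantly worse. The first row is met, the second follows from it, and the third fails. No sentence says which governs.

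**2. The plan's own sample size, to set the scale**

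Inputs from the Sample size section: 42 per arm, four measurements, within-subject correlation 0.5, two-sided 0.05, 80% power. Assume the analysis compares the mean of the three post-baseline measurements:

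- variance factor = (1 + 2 × 0.5)/3 = 0.667
- SE of d = √(0.667 × 2/42) = 0.178
- at d = 0.5, z = 0.5/0.178 = 2.806, and power = Φ(2.806 − 1.96) = 80.1%

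This reproduces 42 per arm (84 in total) with d = 0.5. The section prints d = .05, which would need 4,187 per arm, so 0.5 is evidently meant. The smallest significant d is 1.96 × 0.178 = 0.349, so a minimum of 0.2 (my reading of the effect-size range) excludes nothing here.

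**3. Two primaries (parents)**

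Assume a true coping effect of +0.5. The chance that one psychosocial measure is significantly worse is Φ(|d|/0.178 − 1.96): 2.5% at 0, 20.1% at −0.2, 39.1% at −0.3 and 80.1% at −0.5. With uncorrelated outcomes, multiply by 0.801 for the chance of being declared effective while significantly worse. At −0.5, for example, 0.801 × 0.801 = 64%. Simulation over outcome correlations of 0 to 0.5 gives:

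| True psychosocial d | Declared effective, rule as written | Declared and significantly worse | Declared, with a no-significant-worsening condition |
|---|---|---|---|
| 0 | 80–81% | 1–2% | 79% |
| −0.2 | 80% | 11–16% | 64–69% |
| −0.3 | 80% | 26–31% | 49–55% |
| −0.5 | 80% | 61–64% | 16–19% |

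The second column barely moves: the declaration does not respond to harm. If both outcomes truly improve by 0.5, the rule passes 91–96% and the condition costs nothing measurable.

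**4. Three measures (adolescents): cost when both psychosocial measures are null**

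Uncorrelated:

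- rule as written: 1 − 0.199 × 0.975² = 81.1%
- with the condition: 0.975² − 0.199 × 0.95² = 77.1%
- loss: 4.0 points

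At correlation 0.5, simulation gives 80.2% falling to 78.5%, a loss of 1.7 points.

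**The case against.** A reader might infer that the trial ignores harm. It does not. All primary outcomes go through the mixed models and the Sample size section specifies a two-sided test, so a worsening would be estimated and tested. Nothing suggests it would go unreported.

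A reader might also infer that the plan would send a harmful course into practice. The documents do not support that. The closing Discussion paragraph, read literally, would block a course that improved coping and worsened wellbeing. Its conjunction may be loose wording, and it does not amend the rule, but it rules out treating the abstract's sentence as the only standard.

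Nor is divergence something the documents lead one to expect. The Background reports that effective coping improves adolescents' psychosocial functioning and reduces distress in parents. It also reports that the earlier randomized trial of the face-to-face course found gains on both coping and psychosocial functioning. The +0.5/−0.5 row is a stress test of the rule, not a forecast.

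Finally, any rule that accepts at least one primary lacks a no-harm clause, and an article may leave detail to a fuller document. The first half is true. The second does not help here, because the article states the criterion itself, and what it states conflicts with its own implementation condition.

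These objections limit the point to the prespecified label and the mismatch between sections. Within those limits it stands.

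**Conclusion.** The point holds in this limited form. The rule allows the course to be called effective on coping alone while its stated goal moves significantly the wrong way, and the three statements on effectiveness and implementation do not agree. That follows from the wording and needs no assumed effect sizes.

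The size is conditional. With a true coping effect of +0.5, the declaration rate is about 80% whether the true psychosocial effect is 0 or −0.5. At −0.3, 26–31% of trials would be declared effective with significant psychosocial worsening. These figures assume normal test statistics, 42 per arm, the post-baseline-mean analysis that reproduces the sample size, and outcome correlations of 0 to 0.5. The table is for two primaries, so it is only illustrative for adolescents.

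The change is worth making because it is cheap and removes a choice that would otherwise be made after seeing the results.

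**What to change.** 1. Reconcile the rule in Statistical analyses, the abstract's implementation sentence and the closing Discussion paragraph, so that one standard for effectiveness and one for implementation are stated and used throughout.
2. Add to the rule: the intervention is not qualified as effective if any psychosocial-functioning primary (YSR or CBCL for adolescents, HADS for parents) is significantly worse than control at two-sided 0.05.

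This takes a few sentences and no new data, visits or participants. When psychosocial outcomes are truly unaffected, the chance of a positive declaration falls by about 1 to 2 points for parents and about 2 to 4 for adolescents.

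The sponsor should not claim more for the condition than it delivers. One measure detects a true worsening of d = 0.2 only about 20% of the time, so with two primaries 64–69% of such trials would still be declared effective. Absence of significant worsening is not evidence of no harm.

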### Sample size

Earlier studies on the effectiveness of *Op Koers* and comparable effect studies showed effects of medium size [32, 53]. Based on a design with four repeated measurements and a within subject correlation of .5, 84 adolescents and 84 parents are needed – 42 in each condition – to detect an intervention effect of medium size (d = .05) over time, at a two-sided .05 significance level and 80% power. Taking into account a dropout of 15% over time, 96 adolescents and 96 parents are needed to achieve the intended power.

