In conclusion, adolescents with CI and parents of children and adolescents with CI are at risk for developing psychosocial problems. Easily accessible online evidence-based interventions are needed. This study aims to contribute to research on effective interventions for adolescents with CI and parents of children and adolescents with CI by investigating two separate group interventions, for adolescents and for parents. If this study shows significant effects of the interventions on improving psychosocial wellbeing and disease related coping skills in adolescents and/or parents, *Op Koers Online* will be implemented in clinical practice.

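### Each intervention counts as effective on any one of two primary outcomes (three instruments for adolescents) at an unadjusted 0.05, so the stated level is not the error rate of the decision

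*Protocol article*

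**What the plan says.** The success rule is in the protocol article under Statistical analyses: "The intervention is qualified as effective if the intervention group improved more over time on one of the primary outcomes than the control group". The sentence ends with the threshold, "at a significance level of 0.05 and at small to medium effect size d [0.2–0.5"]. Neither that section nor any other names a lead outcome, a testing order or an adjustment for several outcomes.

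The Abstract names two primary outcomes, psychosocial functioning and coping with the disease. In Table 2, parents have the HADS and the OKQ. Adolescents have the OKQ plus two instruments in the psychosocial row, "Child Behavior Checklist (CBCL) and Youth Self Report (YSR"), with parent and adolescent as informants.

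Under Sample size, "84 adolescents and 84 parents are needed – 42 in each condition", chosen "to detect an intervention effect of medium size (d = .05) over time", "at a two-sided .05 significance level and 80% power". That is a calculation for one outcome and one test.

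Two places speak of implementation. The Discussion paragraph of the Abstract lets it follow once the intervention is shown to be effective. The closing paragraph of the main Discussion states the condition differently: "If this study shows significant effects of the interventions on improving psychosocial wellbeing and disease related coping skills in adolescents and/or parents".

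**The concern.** A rule that accepts a win on any one of several outcomes gives chance several opportunities. If each outcome is tested at 0.05, that figure describes each test and not the verdict on the intervention. The protocol attaches 0.05 to the verdict and sizes the trial as if there were one test.

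The verdict also drives adoption into practice, and the implementation sentences do not agree. Under Statistical analyses with the Abstract, one outcome is enough. Read literally, the closing Discussion sentence asks for both wellbeing and coping. The same data could therefore satisfy one sentence and fail the other.

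**Working it through.** **Inputs.** From the article: 42 evaluable per arm, two-sided 0.05, 80% power, and "Based on a design with four repeated measurements and a within subject correlation of .5" (Sample size); two primary outcomes per trial, three instruments for adolescents (Abstract, Table 2). Assumed: the correlation between outcomes, which the article does not give, shown here from 0 to 0.9.

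**1. The plan's own sample size.** Take d = 0.5 and the mean of m measurements with correlation 0.5, so SD = √[(1 + (m−1)×0.5)/m], and n per arm = 2 × [SD × (1.960 + 0.842)/d]².
- m = 3 (post-baseline): SD = √(2/3) = 0.816, n = 41.9, so 42 per arm and 84 in total. This is the printed figure.
- m = 4: SD = √0.625 = 0.791, n = 39.2, so 40 per arm and 80 in total.

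The printed d of .05 would need about 3,900 to 4,200 per arm, so it is read here as 0.5. The stated size is thus reproduced by one test of one outcome at two-sided 0.05.

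**2. Error rate of the any-one rule, independent outcomes, no true effect on any.**
- At least one two-sided p<0.05: 1 − 0.95² = 9.75% for two; 1 − 0.95³ = 14.26% for three.
- At least one significant result in favour of the intervention (2.5% per test): 1 − 0.975² = 4.94% for two; 1 − 0.975³ = 7.31% for three.

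**3. Correlated outcomes.** Simulation of equally correlated normal test statistics, 2,000,000 draws per row:

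| Assumed correlation | Two: any p<0.05 | Two: false benefit | Three: any p<0.05 | Three: false benefit |
|---|---|---|---|---|
| 0 | 9.8% | 4.9% | 14.3% | 7.3% |
| 0.3 | 9.5% | 4.8% | 13.6% | 6.8% |
| 0.5 | 9.1% | 4.5% | 12.5% | 6.3% |
| 0.7 | 8.3% | 4.2% | 10.9% | 5.5% |
| 0.9 | 7.0% | 3.5% | 8.4% | 4.2% |

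Every entry exceeds its per-test level (5% or 2.5%).

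**4. Does the effect-size condition protect?** Read the range as a floor of 0.2. The smallest significant d at 42 per arm is 1.960 × SD × √(2/42): 0.349 with SD 0.816 and 0.338 with SD 0.791. Adjusting for baseline would lower it to 1.960 × √(2/3 − 0.25) × √(2/42) = 0.28, still above 0.2. The floor excludes no significant result at this size.

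**5. Power if the level is split.** Power = Φ[0.5/(SD × √(2/42)) − z], with 0.5/(SD × √(2/42)) = 2.806 (SD 0.816) or 2.898 (SD 0.791).
- Level 0.025 (two outcomes), z = 2.241: 71.4% or 74.4%.
- Level 0.0167 (three outcomes), z = 2.394: 66.0% or 69.3%.

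**The case against.** The strongest reply is that the rule is directional. A result favouring the control group can never make the intervention effective, so the false-benefit columns describe the claim. On that count the two-outcome rate stays below 5%. This stands, and it limits the size of the problem. It does not remove it: a two-sided 0.05 test allows 2.5% in the favourable direction, and the rule nearly doubles that when correlation is low. The Statistical analyses section does not repeat the sidedness. Were its tests one-sided at 0.05, independent outcomes would give false-benefit rates of 9.75% and 14.26%.

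It can also be said that an analysis plan may add an adjustment. It may, but it would then have to change a rule that the article already fixes.

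Some stronger readings are tempting, and the article does not support them:
- A reader might infer that the error rate is two to three times the stated level throughout. Two outcomes stay just under twice even when independent (4.94/2.5 = 1.98). Only three instruments approach three times, and only near independence.
- A reader might count three adolescent outcomes as given. The Abstract names two, and Table 2 puts CBCL and YSR in one row. Three applies only if they are tested separately.
- A reader might multiply by the follow-up times as well. The rule speaks of improvement over time within a mixed model, which fits one contrast per outcome. Nothing says that each time point may supply a win.
- A reader might hold that a win on the OKQ alone should not count. The Background makes better coping a trial aim and Table 2 makes it primary, so this is a declared choice.
- A reader might take the closing Discussion sentence as a second formal criterion. It carries no level or effect size and does not define effectiveness. It conflicts with the any-one rule only because the Abstract ties implementation to proven effectiveness, so it is wording to align.

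**Conclusion.** The point holds in limited form. Followed as written, the plan gives each trial's verdict an error rate above the level attached to it. Over assumed correlations of 0.5 to 0, the chance of some two-sided p<0.05 is 9.1–9.8% for two outcomes and 12.5–14.3% for three. The chance of a false claim of benefit is 4.5–4.9% and 6.3–7.3%, against a nominal 2.5%. Both shrink as correlation rises, to 3.5% and 4.2% for false benefit at 0.9. These figures assume no effect on any primary outcome, equal correlations and one test per outcome. The direction of the finding does not depend on which correlation in that range is true; its size does. The two trials are separate, so no adjustment across them is implied.

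**What to change.** Keep the any-one rule, and state that the familywise error is controlled at two-sided 0.05 within each trial. Holm across the primary outcomes does this: two for parents, and two or three for adolescents, depending on whether CBCL and YSR are tested separately. Say which. Name one prespecified longitudinal contrast per outcome. A prespecified fixed order is an acceptable alternative. It keeps 0.05 for the first test, but a later outcome can then no longer succeed alone. Reword the implementation sentences in the Abstract and the closing Discussion to follow the same rule. Settle this before outcomes are compared by arm.

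The cost is power. At the first Holm step and 42 per arm, power per outcome is about 71–74% (two outcomes) or 66–69% (three), not 80%. If the effect is present on more than one outcome, the chance of detecting at least one is higher than that. Restoring 80% per outcome at the first step would take 96–102 evaluable participants per trial for two outcomes, or 106–112 for three. With 15% dropout (N/0.85), that is 113–120 or 125–132 recruited, against the planned 96. If the sponsor keeps the planned size, the protocol should state the lower power.

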### Randomization

With an average of five participants per intervention group, a total of ten intervention groups for both adolescents and parents will be given. Interventions are organized at different time points (in four to six cohorts, dependent on inclusion rates). In each cohort, participants are randomly allocated to the conditions resulting in an equal number of participants in the intervention and waitlist control condition. The randomization is carried out by an independent IT worker from a company for e-health development who administers the website for *Op Koers Online*, using block randomization software.

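### The success criterion states no baseline adjustment: adjusting the sized contrast for T0, with cohort in the model, would raise power from 80% to about 94% with the same participants

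*Protocol article*

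**What the plan says.** - **Criterion** (Protocol article, Statistical analyses): the outcomes go into linear mixed models, and the intervention counts as effective "if the intervention group improved more over time on one of the primary outcomes than the control group". The section does not say whether T0 is a response or a covariate, how time is coded, or which contrast is tested.
- **Sizing** (Sample size): "Based on a design with four repeated measurements and a within subject correlation of .5", with "42 in each condition", "to detect an intervention effect of medium size (d = .05) over time", "at a two-sided .05 significance level and 80% power".
- **Visits** (Study design): T0 is taken before randomisation, T1 after 8 weeks (adolescents) or 6 weeks (parents), T2 at six months and T3 at twelve months. T0 is therefore one of the four measurements.
- **Allocation** (Randomization): "In each cohort, participants are randomly allocated to the conditions", in four to six cohorts, in equal numbers per arm.

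**The concern.** A comparison of improvement over time that counts T0 among the repeated measurements suggests a group-by-time model with T0 as one of the responses. Two questions follow.

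First, several tests fit that description, and they differ widely in power at 42 per arm. The stated 80% belongs to only some of them.

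Second, randomisation makes the expected T0 means equal in the two arms. A model that estimates a separate T0 mean in each arm, as a change score does in effect, does not use that fact and carries avoidable variance. The Discussion itself names recruitment as a threat to power, so precision available from data already collected is worth having.

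**Working it through.** **Inputs.** From Sample size: 42 per arm, two-sided .05, 80% power, four measurements, within-subject correlation ρ = .5. The printed effect, .05, is read as 0.5. It is called medium, and .05 would need about 4,187 per arm with the variance used below. Assumptions added here: equal correlation between all visits, outcome SD of 1, normal approximation, and (unless stated) an effect of 0.5 at each of T1, T2 and T3.

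For a contrast with per-person variance v, SE = √(2v/42) and z = effect/SE. Power is approximately Φ(z − 1.96).

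**1. Reproducing the plan's figure.** The contrast is mean of T1-T3 minus T0.
- v = (1 + 2ρ)/3 + 1 − 2ρ = 0.667 + 1 − 1 = 0.667
- n per arm = 2 × 7.849 × 0.667/0.25 = 41.9, so 42
- SE = √(2 × 0.667/42) = 0.178; z = 2.81; power 80.1%

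The T1-T3 mean without T0 has v = (1 + 2ρ)/3 = 0.667, so at ρ = .5 it gives the same 42.

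**2. Other tests that the wording admits, same 42 per arm.**
- 3-df group-by-time: noncentrality 21 × 0.25 × 1.5 = 7.875; power 65% (64% with the F distribution).
- Linear slope with visits at 0, 2, 6 and 12 months: Σ(t − t̄)² = 84, the fitted slope for this effect is 0.0298 per month, and its variance factor is 0.5/84 = 0.00595. z = 1.77; power 42%. Across the exact visit times and equal spacing, the range is 39% to 58%.
- Change from T0 at a single visit: v = 2 − 2ρ = 1; z = 2.29; power 63%.

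**3. The sized contrast, adjusted for T0.**
- v = (1 + 2ρ)/3 − ρ² = 0.667 − 0.25 = 0.417, a cut of 37.5%
- SE = √(2 × 0.417/42) = 0.141; z = 3.55; power 94.4% (93.9% with the t distribution)
- Effect detectable at 80% power: 2.80 × 0.141 = 0.39, against 2.80 × 0.178 = 0.50 without adjustment

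**4. Sensitivity to the correlation.** For ρ from .3 to .7, power is 93% to 98% with adjustment and 66% to 95% for the change score.

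**5. Sensitivity to the shape of the effect (ρ = .5).**

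| Effect at T1, T2, T3 | Mean T1-T3 minus T0 | Mean T1-T3 adjusted for T0 |
|---|---|---|
| 0.5, 0.5, 0.5 | 80% | 94% |
| 0.3, 0.4, 0.5 | 61% | 81% |
| Linear growth to 0.5 at 12 months | 34% | 50% |
| 0.5, 0.25, 0 | 29% | 43% |

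Under linear growth the slope test has about 70%. The gain from T0 is not tied to averaging: for a single visit, adjustment lowers v from 1 to 0.75 and raises power from 63% to 75%.

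**The case against.** A reader might infer that the success criterion is a different contrast from the one the trial was sized for. The documents do not support that. Change from T0 to the T1-T3 mean is a plain reading of greater improvement over time, it gives 42 per arm exactly, and Sample size and Statistical analyses both speak of an effect over time. The article names neither a slope nor a 3-df interaction, so the 42% and 65% show what other readings would cost and are not the power of the stated plan.

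A reader might also infer that the plan makes T0 a free outcome and so wastes it. That is an inference, because the article does not fix the role of T0. T0 as a response is not a fault in itself: a mixed model with a common T0 mean is about as efficient as covariate adjustment. The article is condensed, and the coding of time, the baseline term and a cohort term may stand in an analysis plan that is not shown. Their absence here is not an error.

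Finally, the averaged contrast is not free. It reports a mean level over T1-T3, and a slope test is stronger if the effect builds steadily. The four-month booster session makes a changing effect conceivable.

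All of this stands. It does not touch the gain from T0: in the table above, the adjusted contrast has more power than the same contrast unadjusted under every effect shape.

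**Conclusion.** The concern holds as a recommendation for a better analysis. It shows no error in the sample size and no bias or inflated type I error. The stated 80% is right for one reading of the criterion and too high for two other common ones (65% and 42% under a maintained effect). Adjusting the sized contrast for T0 lifts power from 80% to about 94% at 42 per arm. This rests on d = 0.5, equal correlations of .5 and a constant effect over T1-T3. The direction of the gain is the same across the correlations and effect shapes checked, though its size varies. Choosing the T1-T3 average over another contrast is a trade-off: it keeps the test that was sized and does well for an effect that appears early and lasts.

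**What to change.** For each primary instrument, name one 1-df test: the arm difference averaged over T1, T2 and T3. Estimate it in a linear mixed model with categorical time and either T0 as a covariate or T0 means constrained equal across arms. Include cohort as a fixed effect, since allocation is done within cohort. Report visit-specific differences as secondary. Settle this before outcome data are compared by arm, and if an analysis plan already exists, confirm that it says so.

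The cost is a change to the analysis plan and the SPSS syntax, with no new data. Four to six cohorts use three to five degrees of freedom. The averaged effect says less about timing, and it has less power than a slope test if the effect grows steadily to 12 months (about 50% against 70%). If the investigators expect that pattern and prefer another contrast, the T0 adjustment should still be made.

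### The success rule gives its effect-size condition as a closed range, d from 0.2 to 0.5, so read literally a significant effect above 0.5 does not qualify as effective

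*Protocol article*

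**What the plan says.** The Statistical analyses section of the protocol article gives the only stated rule for declaring success. The intervention is effective if the intervention group "improved more over time on one of the primary outcomes than the control group", and this must hold "at a significance level of 0.05 and at small to medium effect size d [0.2–0.5" (the bracket closes after 0.5). The two conditions are joined by 'and'. The section does not say how an effect above 0.5 is classed.

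The Sample size section plans each trial "to detect an intervention effect of medium size (d = .05) over time", "at a two-sided .05 significance level and 80% power". The design basis is given as follows: "Based on a design with four repeated measurements and a within subject correlation of .5". The result is "84 adolescents and 84 parents are needed – 42 in each condition", raised to 96 per trial for dropout.

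The closing paragraph of the Discussion says the programme will be implemented if significant effects are shown. It gives no effect-size range.

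**The concern.** A success rule should become easier to meet as the benefit grows. A bracketed range with a ceiling does the reverse once the effect passes 0.5. The ceiling also sits at the effect the trials were planned for: the rule's own wording pairs small with 0.2 and medium with 0.5, and the sample size is set for a medium effect.

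Two things are at stake. First, a significant d of 0.6 would support implementation under the Discussion but would not be called effective under the Statistical analyses section. Second, if the wording is settled only after the data are seen, the success criterion has been chosen post hoc, however sensible the choice.

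The lower end raises a smaller question: whether requiring d of at least 0.2 adds anything to requiring significance at this sample size.

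**Working it through.** **Inputs from the protocol article.** Two-sided alpha 0.05, power 80%, four measurements, correlation 0.5, 42 evaluable per arm (Sample size); 96 recruited, so 48 per arm at 1:1 allocation (Sample size, Randomization); success range 0.2 to 0.5 (Statistical analyses).

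**Assumptions not in the article.** The outcome is scaled to SD 1 at each time point, the correlation ρ is the same between all time points, and the normal approximation applies. The variance factor f depends on the estimator, which the article does not fix, so several are shown.

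**Step 1: reproduce the 84.** n per arm = 2f(1.96 + 0.8416)²/d². For the mean of the three post-baseline measures, f = (1 + 2 × 0.5)/3 = 0.667. With d = 0.5, n = 2 × 0.667 × 7.849/0.25 = 41.9, so 42 per arm and 84 in total, which matches. With the printed d of .05 the same formula needs 4,187 per arm. The planned effect must therefore be 0.5; the printed value is a separate slip.

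**Step 2: the ceiling.** SE(d) = √(2 × 0.667/42) = 0.178. The smallest significant estimate is 1.96 × 0.178 = 0.349. For one outcome:

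| True d | P(significant benefit) | P(estimate > 0.5) | P(literal rule met) |
|---|---|---|---|
| 0.5 | 0.801 | 0.500 | 0.301 |
| 0.6 | 0.920 | 0.713 | 0.208 |
| 0.8 | 0.994 | 0.954 | 0.040 |

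The last column is the second minus the third, up to rounding. At true d = 0.5, 0.500/0.801 = 62% of significant results would fall outside the range.

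**Step 3: sensitivity to the estimator (true d = 0.5, 42 per arm).** With the mean of all four measures (f = 0.625) the literal rule is met 33% of the time, against 83% for significance. With the baseline-adjusted post-baseline mean (f = 0.667 − 0.25 = 0.417) the figures are 44% and 94%. The size of the gap varies; its presence does not.

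**Step 4: the floor.** Smallest significant d = 1.96√(2f/n) at ρ = 0.5:

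| Estimator | f | 42 per arm | 48 per arm |
|---|---|---|---|
| Baseline-adjusted mean of three | 0.417 | 0.28 | 0.26 |
| Mean of four | 0.625 | 0.34 | 0.32 |
| Mean of three, or its change from baseline | 0.667 | 0.35 | 0.33 |
| One time point, baseline-adjusted | 0.75 | 0.37 | 0.35 |
| One time point, unadjusted | 1 | 0.43 | 0.40 |

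All exceed 0.2, so under the planning inputs a significant benefit on any of these contrasts already clears the floor. This depends on ρ. For the baseline-adjusted mean, f = (1 + 2ρ)/3 − ρ². At 48 per arm and ρ = 0.78, f = 0.853 − 0.608 = 0.245 and the smallest significant d is 1.96√(2 × 0.245/48) = 0.198, below the floor. At 42 per arm this happens at ρ of about 0.81. For change from baseline it happens at about 0.82 (48 per arm) and 0.84 (42 per arm).

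**The case against.** The strongest reply is that nobody would apply a ceiling. The bracket most naturally supplies numbers for the words small and medium, and the Sample size and Discussion sections both read as though a larger effect would be welcome. This stands as a judgement of intent: a cap was very probably not meant. It does not remove the fault, because the sentence is the stated decision rule and supports more than one reading (a closed range, a lower bound of 0.2, or a threshold somewhere between 0.2 and 0.5).

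Three stronger readings are tempting, and the documents do not support them.

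- A reader might infer that the trials have only 30% power. They do not. The stated 80% refers to significance. The 30% arises only under the literal ceiling, one outcome and an assumed variance factor. The rule also allows success on any one primary outcome. With two independent outcomes, each at true d = 0.5, the literal rule would be met with probability 1 − 0.70² = 51%.
- A reader might infer that the 0.2 floor can never matter. Step 4 shows that it can at a high correlation. It can also matter if significance comes from an overall group-by-time test: a gain at T1 that later fades could be significant while d at T3 is below 0.2.
- A reader might count the undefined d as an omission. The article is condensed and the analysis plan is not shown, so the definition may exist there.

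A floor that is redundant under the planning inputs is also harmless in itself.

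**Conclusion.** The point holds as a fault in the wording of the success rule. As written, a significant effect above 0.5 does not qualify. That conflicts with a sample size that fits only d = 0.5 and with a Discussion that ties implementation to significant effects without a range.

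The illustrative size is about 30% for the literal rule against 80% for significance alone at true d = 0.5. It rests on one outcome, 42 per arm, correlation 0.5 and the mean of three post-baseline measures; the other two estimators in Step 3 give 33% and 44%. These figures show how far the literal text departs from the plan and do not forecast the trials' results.

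The 0.2 floor adds nothing at the planned size and correlation, where the smallest significant d is about 0.26 to 0.43. That is conditional on those inputs and on the test used. Design, sample size and data collection are unaffected.

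**What to change.** Replace the range with a lower bound, for example: *significant at 0.05, with a between-group d of at least 0.2*. In the same place, or by reference to the analysis plan, state the contrast (time point or average) and the SD that d refers to. Report d with its 95% confidence interval, so that relevance is judged on the interval rather than on a floor that significance probably already guarantees.

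The cost is one sentence, with no change to design, sample size or data collection. It should be dated before outcome data are examined.
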